#### Physical examination

The physical examination in the intervention (PTWD) and comparison group (KYS) will be administered at T0, T2, and T3, and will consist of a standardized measurement of weight, height, waist and hip circumference, blood pressure, and heart rate. An anthropometrical protocol will be used for these measurements. We will monitor the execution of this procedure.

#### Blood and urine samples

In the Netherlands, HbA1c levels and fasting plasma glucose of diabetic patients are measured every three months. An extensive analysis of blood and urine samples is performed at least once a year [39]. For T0, T2, and T3, we will collect these data from the participants' medical records. More specifically, we will collect:

• Fasting plasma glucose, HbA1c, total cholesterol, high-density lipoprotein (HDL) cholesterol, triglycerides, creatinine, and creatinine clearance, glomerular filtration rate calculated according to the Modification of Diet in Renal Disease Study (MDRD equation)

• Microalbuminuria

In addition, we will use medical records to collect information on the participants' medication use and diabetes-related complications: retinopathy, cataract, kidney failure, microalbuminuria, myocardial infarction, angina pectoris, transient ischaemic attack (TIA), cerebrovascular accident (CVA), claudicatio intermittens, diabetic ulcers, amputation, polyneuropathy, and sensitivity problems in the feet.

#### Qualitative study

We will perform a qualitative study to gain in-depth understanding of the key mechanisms of PTWD: changes in the psychosocial mechanisms in the immediate social environments of the participants. We will administer semi-structured qualitative interviews with PTWD and KYS participants. Topics will include overall experiences with the intervention, perceived changes in the immediate social environment (psychosocial mechanisms and social support), and perceived benefits of the intervention regarding coping skills and DSM.

#### Process evaluation

The aim of the process evaluation is to gather in-depth information regarding the fidelity and feasibility of PTWD and KYS. Data collection will take place during the entire intervention period. We will study the journals and files of the group leaders, in which they will record the intervention's implementation and progress. In addition, we will regularly observe group meetings, and we will administer a questionnaire and semi-structured in-depth interviews to the group leaders and the participants.

#### Cost-effectiveness

For both PTWD and KYS, we will calculate the organizational costs (e.g. expenses incurred during the intervention, such as hiring group leaders and locations and developing intervention materials), non-medical costs (e.g. expenses incurred by participants because of their participation in the intervention, such as travel expenses), and medical costs (e.g. medical expenses incurred by participants during the intervention, such as the medication they used and visits to their GPs). We will also compare these costs with an estimation of the expenses incurred by the patients in the standard care group.

### Statistical analyses

#### Assessment of effect

Descriptive statistics will be applied to describe the study population at baseline. To determine the effect of the intervention on HbA1c levels and diabetes-related quality of life and to follow individual change over time, we will use generalized linear mixed models. Potential confounders and effect modifiers (e.g. depression, gender, and ethnicity) will be investigated. We will further examine predictors (including intervention-related predictors) of a decrease in HbA1c levels and an increase in diabetes-related quality of life. If necessary, we will use propensity scores to estimate the effects [51,52]. The level of significance is set at p < 0.05.

The analyses of the qualitative data (semi-structured in-depth interviews with the participants) will be done by two researchers using MAXQDA 10, a programme for qualitative data analysis. We will construct an initial conceptual framework based on the theoretical assumptions of the intervention. The data will be coded according to this framework using an inductive approach to also include other aspects related to the identified themes and concepts. Next, we will sort and synthesize the data using thematic charting and further analyse the data by detecting patterns and developing explanations [53,54].

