#### Group meetings for diabetic patients

The diabetic patients will participate in group meetings (ten persons per group) for ten months. In Phase 1 (months 1-3), the participants will be provided with the basic 'tools' they need to manage their diabetes. This phase focuses on creating positive outcome expectations [26,31] and moral norms [28,32], increasing knowledge, skills [26], and self-efficacy [26,31], stimulating social support [33], and recognizing and dealing with psychosocial mechanisms that hinder optimal DSM, such as peer pressure and existing social norms [20,31]. In Phase 2 (months 4-10), the participants will learn how to put the tools they gathered in Phase 1 to use. They will develop and train DSM skills until they have a solid set of coping skills [28,29,34], which will enable them to optimally manage their diabetes in the long term.

To reach these behavioural goals and change the determinants associated with them, we chose strategies that would fit our target population and their specific needs regarding information processing. For example, by engaging the participants in an interactive diabetes quiz, we aim to increase their practical knowledge about diabetes. We aim to increase DSM skills and self-efficacy through a 'letter of the week', in which a fictitious diabetic patient presents a problem and asks the group members for advice. To increase awareness about barriers to DSM (Phase 2), the participants will monitor their own behaviour with the help of specially designed diaries. Through participatory problem-solving and rehearsal situations, we aim to improve the participants' skills and self-efficacy to overcome these barriers. Due to the large number of behavioural goals, in Additional files 1 and 2 we present a representative summary of the behavioural goals, the determinants addressed, and the strategies used in Phases 1 and 2.

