### Matching, blinding, recruitment, and informed consent

For the intervention to be successful, it is important that the participants live near each other. Therefore randomization is impossible. Therefore, the intervention and comparison group will be matched according to ethnicity, gender, and organization of diabetes care. Blinding the general practitioners (GPs) is impossible due to the nature of this study.

Recruiting people and maintaining participation in lower SE groups in intervention studies is difficult due to a low level of trust and insufficient understanding of the study and study procedures [35-38]. To increase trust and understanding, the eligible patients will be invited to a 'welcome meeting' about PTWD or KYS by their GP, a person they trust and respect. For people who do not speak Dutch, we will organize meetings in their mother tongue. At the welcome meetings, the eligible patients will receive detailed information about the study procedures. They will also take part in one of the intervention components (in PTWD groups, a short version of the game about nutrition, in KYS groups a short version of the diabetes quiz) to get an idea of what the intervention will be like. They will also meet their group leaders and the other patients and will see the intervention location, which we hope will lower barriers to participation.

At the end of the welcome meeting, the participants have two weeks to consider their participation. After two weeks they will be asked to sign an informed consent form in which they agree to participate in the intervention and give their consent for the study procedures. The informed consent form will be read to the diabetic patient and further explained if necessary. People who do not speak Dutch will receive the information in their mother tongue.

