### Sample size calculation

The primary outcome measure is the decrease in HbA1c at 16 months. A decrease of 0.5% in the intervention group compared to the comparison group will be seen as a difference that is clinically relevant. This means that at a statistical significance of 5% and a power of 80%, we will need 92 participants in both the intervention and the comparison group. Bearing in mind a dropout rate of 40%, we will need to include 128 people in both the intervention group and the comparison group.

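### The sample size makes no allowance for clustering by peer group, and the analysis text names no group level, although both programmes are delivered in groups

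*Protocol article*

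**What the plan says.** *Sample size.* Protocol article, Sample size calculation: "The primary outcome measure is the decrease in HbA1c at 16 months". The target is set by "A decrease of 0.5% in the intervention group compared to the comparison group will be seen as a difference that is clinically relevant", and the requirement is worked out "at a statistical significance of 5% and a power of 80" per cent: "we will need 92 participants in both the intervention and the comparison group". Then: "Bearing in mind a dropout rate of 40%, we will need to include 128 people in both the intervention group and the comparison group". No SD, group size, ICC or design effect appears among the inputs.

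*Delivery.* Group meetings for diabetic patients: "The diabetic patients will participate in group meetings (ten persons per group) for ten months". The same section describes exchange of advice and contact between members outside the meetings as part of the method. The section on Know your Sugar describes six weekly group meetings with room to exchange support, and gives no group size. The section on matching and recruitment explains the lack of randomization by the fact that "it is important that the participants live near each other", and has patients invited by their GP.

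*Analysis.* Assessment of effect gives the mixed model two purposes: estimating the intervention effect on HbA1c and quality of life, and "to follow individual change over time, we will use generalized linear mixed models". It mentions confounders, effect modifiers, predictors and propensity scores. It does not mention peer group, group leader, practice or neighbourhood, and it does not give the random-effects structure.

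**The concern.** Each participant's programme is fixed by the group he or she joins, so the PTWD versus KYS contrast lies wholly between peer groups. Members of one group share meetings and a neighbourhood, and PTWD is meant to work by members influencing one another. A within-group correlation of exactly zero would sit badly with the trial's own theory.

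Two things are at stake. First, a sample size built from individuals alone overstates power whenever the correlation is positive. Second, a mixed model with only a participant-level random effect accounts for repeated measures within a person but not for similarity between members of a group. Its standard error for the programme contrast would be too small. This contrast carries the primary result, on which the Discussion makes wider implementation depend.

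**Working it through.** **Inputs from the document:** difference 0.5; significance 5% (sidedness not stated, two-sided taken); power 80%; 92 evaluable and 128 enrolled per arm; PTWD groups of ten.

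**Assumptions:** ICC 0.01 to 0.10; KYS groups either of ten or not clustered at all; SD as implied by the stated 92.

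**Step 1, the plan's own figure.** The SD is missing, so 92 cannot be reproduced directly. Solving n = 2·SD²·(1.96 + 0.84)²/0.5² for n = 92 gives SD = 0.5·√46/2.80 ≈ 1.21. Forward, SD 1.21 returns 92 and SD 1.20 returns 91. The stated figure is thus what the ordinary two-sample formula for independent observations gives at SD of about 1.21.

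**Step 2, design effect.** DE = 1 + (m − 1)·ICC, with m members per group. If only PTWD is clustered and the arms are equal, the variance of the difference is inflated by (DE + 1)/2.

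**Step 3, consequences.**
- Evaluable n needed per arm = 92·DE.
- Power at 92 per arm = Φ(0.5/(1.21·√(2·DE/92)) − 1.96). With DE = 1 this is Φ(0.84) = 80%.
- Type I error if groups are ignored = 2·(1 − Φ(1.96/√DE)).

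| Case | ICC | Inflation | n needed per arm | Power at 92 | Type I error if no group term |
|---|---|---|---|---|---|
| Both arms, m = 10 | 0.01 | 1.09 | 101 | 77% | 6.0% |
| | 0.02 | 1.18 | 109 | 73% | 7.1% |
| | 0.05 | 1.45 | 134 | 64% | 10.4% |
| | 0.10 | 1.90 | 175 | 53% | 15.5% |
| Both arms, m = 6 | 0.01 | 1.05 | 97 | 78% | 5.6% |
| | 0.02 | 1.10 | 102 | 76% | 6.2% |
| | 0.05 | 1.25 | 115 | 71% | 8.0% |
| | 0.10 | 1.50 | 138 | 63% | 11.0% |
| PTWD only, m = 10 | 0.01 | 1.045 | 97 | 78% | 5.5% |
| | 0.02 | 1.09 | 101 | 77% | 6.0% |
| | 0.05 | 1.225 | 113 | 72% | 7.7% |
| | 0.10 | 1.45 | 134 | 64% | 10.4% |

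The m = 6 rows represent groups of ten after the planned 40% dropout.

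**Step 4, number of groups.** 128/10 = 12.8, so about 13 PTWD groups. The number of KYS groups cannot be derived. These are normal approximations; with so few groups, a correct test would also lose some power through its degrees of freedom.

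**Step 5, what is not part of this point.** 128 is about 92 × 1.4 = 128.8, whereas 40% dropout requires 92/0.6, which rounds up to 154. Enrolling 128 leaves 128 × 0.6 ≈ 77 completers and power of about 73% with no clustering at all. That shortfall is a dropout matter. The table is therefore computed at the stated 92, so that it shows the effect of clustering alone.

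**The case against.** A reader might infer that the planned model treats participants as independent and that the trial's p-values will be too small. The document does not support this. The sentence on the mixed model also names estimation of the intervention effect, and it states no random-effects structure. A generalized linear mixed model can carry a peer-group effect. Random terms and degrees-of-freedom methods are commonly left to a full protocol or SAP, neither of which is shown. The type I error column is therefore conditional on no group term being fitted and a positive ICC.

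A reader might also take 92 as proof of an independence assumption. It is not, because the SD is missing. SD 1.0 gives 63, and 63 × 1.45 = 91.35 also rounds up to 92. Nothing in the text supports that reading, however, since no clustering input is listed.

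Other limits stand. The group size of ten is stated for PTWD only. The document does not say that a peer group shares one GP practice, or how leaders map to groups. The outcome is a decrease in HbA1c and the Discussion promises control for baseline differences, so stable differences in level between neighbourhoods are partly removed and the relevant ICC is the one for change. Correlation created by interaction within groups would remain. At ICC 0.01 the effect is small.

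None of this answers the sample-size point. The article lists its inputs and draws 92 from them, and power is a design matter that a later analysis plan cannot restore.

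**Conclusion.** The point holds for the sample size and conditionally for the analysis. The calculation shows no allowance for clustering in a trial whose programmes are group-delivered, so 80% power is overstated for any positive within-group correlation. At the stated 92 per arm, power would be about 77% to 53% with groups of ten in both arms, or about 78% to 64% if only PTWD is clustered. These figures rest on an assumed ICC of 0.01 to 0.10, an implied SD of about 1.21 and, for the first range, an assumed KYS group size.

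For the analysis, the text names individual change as the only repeated structure and leaves the group level unstated. Should no group term be fitted, type I error would be about 5.6% to 11.0% (six per group) or 6.0% to 15.5% (ten per group) with clustering in both arms, and about 5.5% to 10.4% if only PTWD is clustered. That the term is absent is not established.

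**What to change.** 1. In Assessment of effect, specify a random effect for peer group in both PTWD and KYS in the primary mixed model, in addition to the participant effect. Add GP practice or neighbourhood if several groups share one. If baseline is modelled as a repeated outcome, let the group effect act on change over time as well, since a group intercept alone captures only stable differences in level.
2. Use small-sample degrees of freedom, for example Kenward-Roger, given about 13 PTWD groups.
3. In Sample size calculation, state the SD, the group size in each programme and an ICC range, and restate power with the resulting design effect. Correct the dropout inflation separately, so that the two shortfalls can be told apart.

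The cost is modest. Group membership should be known from delivery, so the main work is model wording and keeping a group identifier in the data. Confidence intervals become somewhat wider, and the stated power falls unless more groups are recruited.

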#### Assessment of process

All qualitative data (journals and files of the group leaders, semi-structured in-depth interviews) will be analysed with MAXQDA according to the principles of content analysis [53]. The quantitative (semi-structured questionnaires) data will be analysed with SPSS using descriptive statistics.

#### Cost-effectiveness

The costs of the interventions will be described and compared to the quality-of-life outcome measures.

## Discussion

Growing evidence suggests that in addition to social support, other psychosocial mechanisms in the immediate social environments of diabetic patients such as social influence and social engagement have a major influence on DSM as well. Diabetic patients in lower SE groups in particular seem to be confronted with strong psychosocial mechanisms that have an adverse effect on their DSM and seem to experience more difficulties in coping with these mechanisms. Therefore, to improve DSM among these groups it seems necessary to target all psychosocial mechanisms in the immediate social environment that impact their DSM: social support, social influence, and social engagement.

PTWD is, to our knowledge, the first culturally sensitive social network intervention targeted to lower SE groups that aims to stimulate the long-term social support of peers and the immediate social environment, and to target existing psychosocial mechanisms through which the immediate social environment negatively influences DSM. The DISC Study evaluates the effectiveness of PTWD.

A limitation of this study might be that blinding the GPs during the study was impossible. Another limitation that might bias the comparability of the groups is that it was impossible to randomize the intervention and comparison groups due to characteristics of the intervention. We think that the chance of selection bias will be small, because both the intervention and the comparison groups will be invited to a lifestyle intervention. We will record all reasons for participation and non-participation among our respondents, which will enable us to assess any selection bias. In addition, we will control for differences between the groups at baseline and take these differences into account during the analyses.

The present study will be strengthened by the use of data triangulation. We will use a wide variety of sources of information such as questionnaires, semi-structured qualitative interviews, medical records, physical examinations, and the journals and files of the group leaders. This will increase the validity of this study. Moreover, the qualitative semi-structured interviews will reveal in-depth information about lower SE groups that is lacking to date.

This study will provide insights into how to enable diabetic patients in lower SE groups to optimally manage their diabetes by intervening in the psychosocial mechanisms in the social environment that negatively impact their DSM: social support, social influence, and social engagement. If PTWD is effective in lowering the HbA1c levels of the participants and improving their diabetes-related quality of life, further implementation will be considered. PTWD could be implemented in the context of a GP practice, where it could contribute to more efficient diabetes care for diabetic patients in lower SE groups.

## Abbreviations

DISC: Diabetes in social context study; SE: Socioeconomic; DSM: Diabetes self-management; PTWD: *Powerful Together with Diabetes*; KYS: *Know your Sugar*; NIGZ: Dutch national institute for health promotion and disease prevention; GP: General practitioner; DPSI: Diabetes problem-solving interview; DSSQ: Diabetes social support questionnaire; TpB: Theory of planned behaviour; BMI: Body mass index; HbA1c: Haemoglobin A1C; SO: Significant others; AMC: Academic medical center; TIA: Transient ischaemic attack; CVA: Cerebrovascular accident.
